#### Sample Size Calculation

Patient participants will be grouped into 1 of 4 arms (as determined by the unit they were discharged from) in both the baseline (pre-intervention) and postintervention periods. Our primary outcome, CTM-3, is scored as a continuous variable (0 to 100%) based on a published algorithm [77]. THP pilot data with 107 patients showed a baseline CTM-3 score of 74% (SD 21.4; unpublished). Our sample size calculation is based on an anticipated 13% to 14% increase in CTM-3 score and a standard deviation of 21.4 (derived from our previous studies of Care Connector). To ensure analysis for each of the 8 subgroups to be significant, we required a higher sample size than would be required in typical drug trials where randomization occurs at the individual level. As such we will recruit 33 to 38 patients per group; 8 groups in baseline (264 to 304) and 8 groups in intervention (264 to 304) for a total of 528 to 608 (based on *P*=.05 and power of .80).

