### Study Design

We will conduct a nonrandomized controlled trial to understand the impact of the intervention. For each site (SHS and THP) and each service (acute medicine and rehab), half of the participating wards will be designated as control while the other half will be designated as intervention (4 wards per hospital for a total of 8 wards). Quasi-experimental (or nonrandomized) design is often used in medical informatics evaluation due to insufficient sample size for cluster-randomized design [60] and complexity of intervention [61]. We have chosen to designate intervention wards together with operational leaders at each organization rather than randomize wards to increase the chance of successful implementation. While this could introduce selection bias into the study, it is felt this risk is worthwhile given that one important barrier to adoption of information communication technologies in hospitals is lack of readiness for implementation [62-64]. If clinical units that are not ready to take on a new technology implementation are randomized into the intervention group, we may experience a feasibility barrier that could derail the study before it begins. Our mixed-methods approach has been designed to capture important characteristics of the included clinical wards so that any potential selection bias can be understood.

General medicine units at both organizations serve a complex and clinically diverse population, with a median age of 73 (IQR 57-84) years and a median of 6 (IQR 3-9) coexisting medical conditions [65]. They care for patients with a wide variety of diagnoses (more than 200 distinct diagnoses) with the top 10 diagnoses comprising 36.2% of hospitalizations [66]. Rehabilitation services across the two organizations admit patients due to stroke, musculoskeletal concerns, and complex medical needs. At THP, services are not diagnosis-based; at SHS, however, patients are clustered on wards with specialized services.

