#### Implementation Measures

Implementation relates to the processes required to put an intervention or new model of care into use [79]. An implementation lens identifies context and process variables likely to influence intervention outcomes, known to be important in studies of digital health interventions [83]. Context and process data will additionally support the development of a scale and spread strategy [84] and is consistent with a developmental evaluation approach [59]. We will adopt the Consolidated Framework for Implementation Research (CFIR) [79], which compiles constructs that have been associated with effective implementation of complex interventions (see Figure 3 [79]).

An embedded ethnographic comparative case study methodology will be adopted, aligned with the case study approach of Yin [85] and the ethnographic approach to evaluating technology of Greehalgh [86]. Each site/service combination is considered a single case (8 cases total). Interviews with patients and caregivers (subset of 5 patients and caregivers from each unit, 40 patients and 40 caregivers total) and focus groups with providers and managers (6 to 8 participants per group [87]) will be conducted, along with a review of relevant organizational documents (eg, annual reports and vision statements) and observations of provider interactions and patient-provider interactions (eg, rounds, care planning meetings, clinic visits).

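### The sample size section speaks of 4 undefined arms but sizes 8 ward groups per period, and 33 to 38 patients per group generally do not give each group the stated 80% power

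*Protocol article*

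**What the plan says.** All of the sizing is in one paragraph of the protocol article, Sample Size Calculation. It first states that "Patient participants will be grouped into 1 of 4 arms (as determined by the unit they were discharged from"), and applies this to each of the two periods. It then gives the reason for the size chosen: "To ensure analysis for each of the 8 subgroups to be significant". The effect and spread are "an anticipated 13% to 14% increase in CTM-3 score and a standard deviation of 21.4", with a pilot baseline of 74%. The result is that "we will recruit 33 to 38 patients per group; 8 groups in baseline (264 to 304) and 8 groups in intervention (264 to 304"). The sum over both periods is given as 528 to 608 patients, at P=.05 and power .80.

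Study Design describes two sites, two services at each, and half the wards in each site and service assigned to the intervention: "4 wards per hospital for a total of 8 wards". The same section names the main contrast as a difference in differences between control and intervention wards across the two periods. The Phase 2 data analysis section plans mixed-effects models, with each service examined separately as a sensitivity analysis.

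Implementation Measures has a similar mismatch of counts: "Each site/service combination is considered a single case (8 cases total"), although two sites by two services make four combinations.

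**The concern.** Grouping patients by discharge unit gives 8 groups, because there are 8 wards. Four groups could be service by treatment, with the sites pooled. They could also be site by service, in which case each arm would mix treated and control wards. The article does not say which, or whether 4 is simply a slip.

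The label also bears on the power statement, which is the only one for the primary outcome. The paragraph promises adequate power for each of 8 subgroups but does not name the comparison: before against after within a ward, intervention against control, or the difference in differences. A reader will take from it that a result for a single ward or service can be interpreted at 80% power. If that power is not there, a null finding in one service would be over-read as absence of effect, and the service-by-service sensitivity analysis would be trusted more than it should be.

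**Working it through.** **Inputs.** From Sample Size Calculation: SD 21.4, baseline 74, increase 13% to 14%, 33 to 38 per group, 8 groups per period, alpha 0.05, power 0.80. From Study Design: 8 wards, difference in differences. Assumptions: two-sided test (the article does not state sidedness), equal SD in all cells, independent patients, no clustering, no dropout.

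**1. The plan's totals.** 8 × 33 = 264 and 8 × 38 = 304 per period; doubled, 528 and 608. These reproduce. The abstract's 300 per period is 300/8 = 37.5 per group, which also fits 8. Four arms in two periods would give only 4 × 2 × 33 = 264 to 4 × 2 × 38 = 304 in all.

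**2. The plan's size per group.** For two independent means, n = 2 × (1.960 + 0.842)² × SD² / d².
- d = 14: n = 36.7, so 37 (38 by t-test). This matches the stated upper figure.
- d = 13: n = 42.5, so 43 (44 by t-test). The stated lower figure is 33.
- A two-sided t-test returns 33 and 38 for differences of 15 and 14 points, not 13 and 14.

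**3. Power within one ward, before against after (two-sided t-test).** The standard error is 21.4 × √(2/n): 5.27 at n = 33 and 4.91 at n = 38.

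| True rise | n = 33 | n = 38 |
|---|---|---|
| 13 points (absolute) | 68% | 74% |
| 14 points (absolute) | 75% (0.745) | 80% |
| 0.13 × 74 = 9.62 points (relative) | 44% | 49% |
| 0.14 × 74 = 10.36 points (relative) | 49% | 55% |

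Only the most favourable corner, 14 absolute points at 38 per group, reaches 80%.

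**4. Difference in differences within one site and service** (one intervention and one control ward, two periods, four cells of n; normal approximation). The standard error is 21.4 × √(4/n): 7.45 at n = 33 and 6.94 at n = 38.
- 13 points, n = 33: 13/7.45 − 1.96 = −0.215, power 42%.
- 14 points, n = 38: 14/6.94 − 1.96 = 0.057, power 52%.
- For 80% power, n = 4 × (2.802 × 21.4 / d)² gives 86 per cell at 13 points and 74 at 14 points.

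**5. Difference detectable with 80% power.**
- Within-ward before-after (t-test): 15.0 points at 33 and 13.9 at 38.
- Difference in differences: 2.802 × 7.45 = 20.9 points at 33 per cell, and 2.802 × 6.94 = about 19.5 at 38 per cell.

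**The case against.** The strongest reply is that the unit of power is stated. The paragraph ties the sizing to 8 subgroups and to a number per group. The totals, the 8 wards, the abstract's 300 per period and the 40 interviewed patients at 5 per unit all fit 8. Four arms of two wards each could nest within 8 wards. All of this stands: the 4 is an undefined label, not proof that two power units compete, and the totals contain no arithmetic error.

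A reader might go further and infer that the study was really sized for 4 arms of 66 to 76, since a relative increase of 13% to 14% needs 78 to 67 per group, close to two pooled wards. The documents do not support that. They nowhere give 66 to 76 or attach 80% power to arms, and the match is not exact (79 and 68 by t-test). The inference also depends on the relative reading. The score and its baseline are both given in percent, so absolute points are at least as natural, and on that reading 14 points returns the stated 38. For the same reason, 44% to 55% should not be quoted as the only power per ward.

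Sidedness is the other defence. With a one-sided 5% test, 13 points at 33 has 79.5% power and 14 points at 38 has 88.6% (normal approximation), so the within-ward claim on the absolute reading would roughly hold. However, the one-sided sizes for 13 and 14 points are 34 and 29, not the stated range. The difference in differences would still fall short: 13/7.45 − 1.645 = 0.10 and 14/6.94 − 1.645 = 0.37, or 54% to 64%.

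Finally, the figure showing the within- and between-group analysis is not available here and may identify the groups. That would settle the label but not the power.

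**Conclusion.** The point holds in two parts. First, the 4 arms are undefined and unreconciled with the 8 groups counted in the same paragraph; this is a wording fault, and 528 to 608 remains correct. Second, the stated 80% power for each of the 8 subgroups is generally not delivered by 33 to 38 per group. Power is 68% to 80% for a within-ward before-after rise of 13 to 14 absolute points, 44% to 55% if the increase is relative to 74%, and about 42% to 52% for the planned difference in differences within one site and service at 13 to 14 points.

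These figures assume SD 21.4, a two-sided 5% test, complete data and no clustering; dropout would lower them. They concern single wards or a single site and service. They do not show that the pooled analysis over all 8 wards is underpowered.

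**What to change.** In Sample Size Calculation:
- Replace the 4 arms by 8 wards (4 intervention, 4 control), and bring the count of cases under Implementation Measures into line.
- State whether 13% to 14% means absolute points or is relative to the 74% baseline, and state the sidedness of the test.
- Name the comparison to which the power applies.
- Restate the difference detectable with 80% power, before clustering: 15.0 to 13.9 points for a within-ward before-after comparison at 33 to 38 per group, and about 20.9 to 19.5 points for a difference in differences at 33 to 38 per cell (both two-sided).
- Drop the claim that each of the 8 subgroups has 80% power for a 13% to 14% increase.

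Keeping 4 arms and attaching 80% power for 9.6 to 10.4 points to 66 to 76 per arm would not be a sound repair. Those numbers detect 10.5 to 9.8 points in a simple two-group comparison, and 14.8 to about 13.8 in a difference in differences with that many per cell.

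The cost is one reworded paragraph and a less favourable stated power per subgroup. Recruitment is unchanged.

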We will collect baseline data from all wards (control and intervention) during phase 1 while co-design is ongoing and the intervention has not been deployed. During phase 2, after co-design is complete, the co-designed technology intervention and workflow will be rolled out to only the intervention wards. We will then collect data (identical to what was collected at baseline) from all wards (control and intervention) to understand the impact of technology by examining the differential change in control and intervention wards between baseline and intervention periods (difference in differences approach).

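### The sample size of 33 to 38 per group does not follow from its stated inputs under a two-sided test, and it does not give each subgroup 80% power for the planned difference in differences

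*Protocol article*

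**What the plan says.** The Sample Size Calculation section of the protocol article sets the primary outcome on a 0 to 100 scale: "Our primary outcome, CTM-3, is scored as a continuous variable (0 to 100". Pilot data give a mean of 74 and an SD of 21.4. The effect and spread are then fixed: "Our sample size calculation is based on an anticipated 13% to 14% increase in CTM-3 score and a standard deviation of 21.4". The level of inference is the subgroup: "To ensure analysis for each of the 8 subgroups to be significant, we required a higher sample size", which the article says is larger than a typical drug trial with individual randomization would need. The result is that "we will recruit 33 to 38 patients per group; 8 groups in baseline (264 to 304) and 8 groups in intervention (264 to 304", a total of 528 to 608, at P=.05 and power .80. The section gives no formula, sidedness, ICC, design effect or allowance for loss.

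Study Design places 4 wards in each of 2 hospitals and splits each site and service evenly, so each site-service has one control and one intervention ward. The effect is to be learned by "examining the differential change in control and intervention wards between baseline and intervention periods (difference in differences approach". The Phase 2 analysis section plans mixed-effects models for clustering and a separate look at each service as a sensitivity analysis.

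**The concern.** Two things do not fit. First, the usual two-sided calculation from the stated inputs does not return the stated range. Second, power is claimed for each subgroup, but the only sizes that return 33 to 38 are for a plain comparison of two means. The planned effect measure contrasts four means, which doubles the variance at the same number per cell.

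The primary outcome is affected. A reader told that each subgroup analysis has 80% power would take a null result in one site-service as evidence of no benefit there. For the planned contrast the chance of detecting the anticipated effect in a single site-service is nearer one half. Meanwhile no power is given for the pooled contrast, which is the one that answers the effectiveness question.

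**Working it through.** **Inputs.** From the Sample Size Calculation section: SD 21.4, effect d = 13 to 14 (read as points on the 0 to 100 scale), alpha .05, power .80, n = 33 to 38 per ward-period group. From Study Design: 8 wards, 4 control and 4 intervention, one of each per site-service. Two-sided testing is assumed first because the article does not state sidedness.

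**Step 1: reproduce the plan's figure.** The totals are correct: 8 × 33 = 264, 8 × 38 = 304, and twice these gives 528 and 608. For the per-group size, n = 2(1.96 + 0.8416)² × 21.4² / d².

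| d (points) | Normal approximation | t test |
|---|---|---|
| 13 | 42.5, so 43 | 43.5, so 44 |
| 14 | 36.7, so 37 | 37.7, so 38 |
| 15 | 32.0, so 32 | 32.9, so 33 |

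The upper figure, 38, matches 14 points. The lower figure, 33, matches neither 13 nor 14. Two unstated readings return both ends:

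- effects of 14 to 15 points, two-sided t test: 38 and 33;
- one-sided .05, normal approximation, 10% loss: 34/0.9 = 37.8, so 38, at 13 points; 29/0.9 = 32.2, so 33, at 14 points.

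Both are unclustered comparisons of two means.

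**Step 2: power of a simple two-group comparison (two-sided t test).**

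| n per group | 13 points | 14 points |
|---|---|---|
| 33 | 68% | 74% |
| 38 | 74% | 80% |

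**Step 3: difference in differences within one site-service.** Four cells of n patients give SE = 21.4 × √(4/n).

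- n = 33: SE = 7.45. Power at 13 points: 13/7.45 − 1.96 = −0.215, so 41%. The 80% detectable difference is 2.80 × 7.45 = 20.9 points.
- n = 38: SE = 6.94. Power at 14 points: 14/6.94 − 1.96 = 0.056, so 52%. The 80% detectable difference is 2.80 × 6.94 = 19.5 points.
- A one-sided .05 test raises these powers to 54% and 64%.
- For 80% two-sided power, n per cell = 4 × (2.80 × 21.4/d)² = 86 at 13 points and 74 at 14.

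None of these figures includes clustering. With one ward per arm, ward-by-period variation cannot be separated from the effect within a site-service.

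**Step 4: difference in differences pooled over 8 wards.** Cells hold 4n = 132 to 152 patients, so SE = 21.4 × √(4/132) = 3.73 to 21.4 × √(4/152) = 3.47. To show sensitivity, multiply the variance by 1 + (n − 1)ρ, where ρ is an assumed ward-by-period correlation. The t reference uses 8 − 2 = 6 df.

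| Assumed ρ | Normal | t, 6 df |
|---|---|---|
| 0 | 94% to 98% | 83% to 92% |
| 0.01 | 86% to 93% | 72% to 82% |
| 0.05 | 58% to 67% | 44% to 52% |

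The low end of each range is n = 33 with 13 points, the high end n = 38 with 14 points. On the normal reference, power drops below 80% once ρ exceeds about 0.017 to 0.029.

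**The case against.** The strongest reply is that the article fixes neither the formula nor the sidedness. It anticipates an increase and says only P=.05, so a one-sided test with 10% loss is possible and returns 33 to 38 exactly. That stands as a possibility, and for the same reason it cannot be asserted that loss was ignored. But the article states neither assumption, the match is off by one with t-based sizes (35/0.9 gives 39, 30/0.9 gives 34), and it is still a two-group comparison.

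A second reply is that the subgroup contrast may be a pre-post comparison within each ward. The 8 groups in each period and the pre-post wording of the Phase 2 analysis section allow this, and power is then 68% to 80%, not 41% to 52%. This is fair. But four of the 8 wards are controls, where no intervention effect is expected, so sizing the study for all 8 to be significant makes no sense on that reading.

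A reader might also infer that the trial as a whole lacks 80% power. The documents do not support this. The pooled contrast is adequate without clustering, with 132 to 152 per cell against 74 to 86 needed by the unclustered normal calculation, and its shortfalls rest on assumed correlations. Nor does the remark about needing more patients than an individually randomized trial contradict itself outright: it may refer to the total, since a two-group trial at these effects needs only about 76 to 88 patients in all.

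**Conclusion.** The point holds in limited form. Under a two-sided test the stated inputs give 44 to 38 per group, not 33 to 38; the planned numbers deliver 68% to 80% for a simple two-group comparison. The promise of 80% power in each subgroup fails for the difference in differences taken within one site-service: 41% to 52% two-sided, 54% to 64% one-sided, before clustering. That result needs no ICC and does not depend on which formula the authors used. It does assume that the subgroup contrast is the one Study Design defines, applied within a site-service.

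Power for the pooled contrast is an open question, because the article gives no ICC. The effect is taken as absolute points, the natural reading of a score given in percent.

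**What to change.** Rewrite the Sample Size Calculation paragraph as follows.

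1. Name the pooled ward-designation by period interaction on CTM-3 as the powered contrast, and give its power for the planned 528 to 608 patients over a range of ICCs labelled as assumed.
2. State the effect in absolute CTM-3 points, the sidedness, and any allowance for loss.
3. Reconcile 33 to 38 with 13 to 14 points. Either report the power actually delivered (about 68% to 80% for a simple two-sided two-group comparison) or give the sizes that match (44 to 38). Do not move the anticipated effect to 14 to 15 points merely to fit the numbers.
4. Replace the claim that each of the 8 subgroups will be significant with a statement that site-service results are descriptive, with a detectable difference of about 20 points.

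The cost is protocol wording and one recalculation. No extra enrolment is asked for. The downside is that the stated power becomes less favourable.

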		**Patient (outcomes)**					
			Transition quality	CTM3^d^		1 to 2 weeks post-discharge	
			Health-related quality of life	AQoL-4D^e^		At 1 and 6 months post-discharge	
			Goal attainment	GAS^f^		As captured by ePRO^g^ (intervention only)	

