### Population and Recruitment

Patients will be recruited at the time of admission to one of the services (acute medicine or rehab) in the study. Patients aged 60 years and over, with CCN defined as presenting with 3 or more chronic conditions from the 16 most prominent in the population: arthritis (except rheumatoid arthritis), chronic coronary syndrome, dementia, hypertension, cardiac arrhythmia, rheumatoid arthritis, asthma, osteoporosis, stroke, depression, chronic obstructive pulmonary disease, acute myocardial infarction, diabetes, congestive heart failure, cancer, and renal failure.

This method is aligned with current and established methods to identify patients with CCN [67-69]. Patients must be slated to be discharged home. As the technology is only currently available in English, patients (or a caregiver) must be able to speak and read English. Patients with mild cognitive impairment will not be excluded if able to provide informed consent and engage with the intervention (independently or with caregiver aid). During phase 1, all recruited patients will receive usual care. During phase 2, recruited patients from the intervention wards will receive the Digital Bridge intervention while those from control wards will receive usual care. Family/caregivers of recruited patients may be invited to participate in qualitative interviews.

As workflow integration is a foundation for implementing technology, all hospital providers on the general medicine and rehabilitation services will be invited to participate. PCPs of recruited patients will be contacted and invited to participate while the patient is still in hospital. Recruited patients may still participate in the study if their PCP does not wish to participate or if they do not have a PCP at the time of study enrollment. Should the PCP choose to join, they will be consented and trained to adopt the technology to support their patients post-discharge if their patients were recruited from the intervention wards during phase 2.

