**Figure 4 figure4:**
[figure not shown]
Within and between group pre-post analysis.

For quantitative outcome measures (eg, CTM-3, relational coordination, AQoL-4D), statistical comparisons between the pre- (baseline) and post- (intervention) data will be made using mixed-effects regression models to account for potential clustering effect of patients from the same service. As this is a complex intervention and local context/implementation factors may affect outcomes, we will perform sensitivity analysis and examine each of the participating services separately. For repeated measures within the same individual, we will use a difference in differences approach (eg, AQoL-4D measured at 0, 2 weeks, 1 month, and 6 months post-discharge). Patients may experience decline in QoL over time in both control and intervention groups for reasons unrelated to the intervention; a lesser magnitude of decline in intervention versus control group may suggest a benefit of the intervention.

For patients who do not complete a study follow-up, we will analyze all available data points. Additionally, understanding the characteristics (via collected demographic and administrative data of this study) of those who do not complete follow-up may inform us of under what conditions and for whom the technology works best.

Qualitative data will be analyzed using an ethnographic case study approach [86], adopting techniques such as interpretive descriptive coding methods and word tables [85] to support the within and cross case analysis as used in previous evaluations and similar case comparisons [33,48]. Two researchers trained in qualitative research will read interview and focus group transcripts and field notes, record key themes, compare, and discuss findings. Both inductive and deductive analysis techniques will be used to identify themes and then conceptually map with the CFIR theoretical framework. NVivo software (QSR International) will be used for qualitative data management.

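### The 80% power for each subgroup is tied to 33 to 38 patients recruited at admission, with no allowance for recruits who give no CTM-3 score after discharge

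*Protocol article*

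**What the plan says.** The Sample Size Calculation section gives its inputs: "Our sample size calculation is based on an anticipated 13% to 14% increase in CTM-3 score and a standard deviation of 21.4". It says what the size is for: "To ensure analysis for each of the 8 subgroups to be significant". It then sets the number as a recruitment target: "As such we will recruit 33 to 38 patients per group; 8 groups in baseline (264 to 304) and 8 groups in intervention (264 to". The range is the same in both periods, the overall target is 528 to 608, and the figures are "based on *P*=.05 and power of .80". It mentions no allowance for loss.

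The Population and Recruitment section fixes when a patient enters: "Patients will be recruited at the time of admission to one of the services (acute medicine or rehab) in the study". At that point discharge home is planned and has not yet happened. Table 1 (Phase 2, patient outcomes) schedules CTM-3 once, "1 to 2 weeks post-discharge". The Phase 2 analysis section says: "For patients who do not complete a study follow-up, we will analyze all available data points".

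**The concern.** A power calculation for a comparison of means counts observed scores. Here the count is of patients recruited at admission, and a hospital stay and a survey window lie between recruitment and the score. The recruits are aged 60 and over with at least three chronic conditions, so some will die or not answer the survey.

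Analysing all available data can help an outcome measured repeatedly, such as AQoL-4D. It recovers nothing for CTM-3, because a patient without the single survey has no CTM-3 data point. If the recruitment number is already the bare number of scores required, the stated .80 assumes that every recruit completes the survey. A null result for one ward or service would then be read against a power that the analysed sample did not have.

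**Working it through.** **Inputs (Sample Size Calculation section).** Difference d = 13 to 14 CTM-3 points; SD 21.4; alpha .05; power .80; n = 33 to 38 per group. Three readings are mine:
- The test is two-sided, because the article does not say.
- The subgroup comparison is between two independent groups of equal size.
- The increase is in points on the 0 to 100 scale. A relative increase on the baseline of 74 would be only 9.62 to 10.36 points and would need 79 or 68 per group.

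**Step 1: reproduce the plan's figure.** The normal formula is n = 2(1.960 + 0.842)² SD² / d², and 2 × 7.849 × 21.4² = 7,189.
- d = 14: 7,189/196 = 36.7, so 37 (t-test 37.7, so 38).
- d = 13: 7,189/169 = 42.5, so 43 (t-test 43.5, so 44).
- d = 15: 7,189/225 = 32.0, so 32 (t-test 32.9, so 33).

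The upper figure, 38, is exactly the uninflated t-test number for 14 points. The lower figure, 33, matches 15 points, which lies outside the stated range. The stated inputs give 37–38 to 43–44 per group, so 33 to 38 does not reproduce as a range.

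**Step 2: power per subgroup comparison (two-sided t-test), without and with loss.** The documents give no loss rate, so 10% to 30% is an assumption. Completed scores per group = n × (1 − loss).

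| Recruited per group, difference | No loss | 10% | 20% | 30% |
|---|---|---|---|---|
| 38, 14 points | 80.4% | 76.0% | 70.8% | 64.8% |
| 38, 13 points | 74.3% | 69.7% | 64.4% | 58.5% |
| 33, 14 points | 74.5% | 69.8% | 64.5% | 58.5% |
| 33, 13 points | 68.1% | 63.4% | 58.1% | 52.4% |

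Completed scores per group at 10%, 20% and 30% loss are 34.2, 30.4 and 26.6 from 38 recruits, and 29.7, 26.4 and 23.1 from 33. At 20% loss, 528 × 0.8 = 422 and 608 × 0.8 = 486 scores remain overall.

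**Step 3: the pooled contrast, for comparison.** In the difference in differences with four wards in each arm-by-period cell, m = 4n(1 − loss) and SE = SD√(4/m). Power is approximately Φ(d/SE − 1.960).
- No loss: 94% to 96% at n = 33 and 96% to 98% at n = 38, for 13 to 14 points.
- 30% loss, n = 33: m = 92.4 and SE = 4.45, giving 83% at 13 points and 88% at 14.

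These figures ignore clustering within wards. No intracluster correlation is given, so they are upper bounds and do not show that the pooled analysis is adequately powered.

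**The case against.** **A reader might infer that the trial as a whole falls below 80% power.** The documents do not support this. The .80 is stated for subgroups, while the design section makes the difference in differences over all wards the main contrast, and the analysis section examines services separately as a sensitivity analysis. Step 3 shows that the pooled contrast tolerates moderate loss if clustering is ignored. What remains is that the article chose its size for the subgroups, so the per-subgroup figure is the power claim it makes.

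**A reader might also infer that any single lost patient takes the power below 80%.** Only 38 per group at 14 points reaches 80% at all; elsewhere, loss deepens an existing shortfall. Even at 38, losing one score per group leaves 79.3% by t-test but 80.3% by the normal formula.

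**Nor does the analysis section contradict the sample size section.** It gives a general handling rule that also covers the 1- and 6-month surveys, and it forecasts no CTM-3 loss.

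**Some routes of loss are inference.** Participants are grouped by the unit they left, so a group could be read as patients already discharged, which would exclude deaths in hospital. Readmitted patients who have used the Digital Bridge keep their data collection schedule. Nothing says that a patient not sent home gives no score. Non-response and death after discharge remain, at unknown rates.

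**A one-sided test would soften the figures.** It needs about 34 to 35 per group at 13 points and 29 to 30 at 14, so 38 would carry some margin. It does not reproduce 33 to 38 either, and the article does not say that it was used.

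**A condensed article may leave an attrition allowance to the full protocol.** That is fair for an omitted detail. Here, though, the article prints the inputs, the power and the recruitment number together, and the top of the recruitment range equals the number of scores needed with no loss.

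**Conclusion.** The point holds for the per-subgroup power. The stated .80 belongs to completed CTM-3 scores and is reached only at 38 scores per group and 14 points (80.4%). At the other ends of the stated ranges, power is 68.1% to 74.5% before any loss. With an assumed 20% of recruits giving no score, it is about 58% to 71% across 33 to 38 recruits and 13 to 14 points.

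These figures rest on a two-sided t-test, SD 21.4, no clustering, equal loss in the groups compared and an assumed loss rate. They do not show that the pooled analysis is underpowered. The correction is worth making because the article offers this power as the reason for its sample size, and subgroup results would be interpreted against it.

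**What to change.** In the Sample Size Calculation section, keep the total and say that the power refers to completed CTM-3 surveys per subgroup. Then restate it at the expected number of completed surveys, for both 13 and 14 points and for both ends of 33 to 38, naming the assumed completion rate. At 20% loss the statement would read about 58% to 71%.

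Two shorter repairs do not work. Relabelling 33 to 38 as completed surveys would still pair 33 with a power of .80 that it does not reach at 13 or 14 points. Recruiting until 38 surveys per group are complete cannot be done within 608, because 16 × 38 = 608 leaves no spare recruit.

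The cost is wording and one recalculated figure, with no change to recruitment. The downside is a less favourable stated power.
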